### Study assessments

Enumeration of CMV DNA copies for the determination of the primary outcome (CMV reactivation) will be carried out by PCR of plasma and urine. This assessment will be performed by the UHB Virology Laboratory using an existing validated assay utilised for clinical samples.

Whole blood will be stained with fluorochrome conjugated monoclonal antibodies to CD3, CD4 and CD28 and analysed via flow cytometry (LSR II Flow Cytometer, DIVA Software; BD) to determine the proportion of CD4 + CD28null cells in peripheral blood. Plasma will be assessed via Luminex technology to determine the soluble markers of inflammation (Table 1). These assays will be validated for precision and reproducibility prior to commencement of the trial (see also the laboratory manual; Additional file 4).

Determination of blood pressure and arterial stiffness will be conducted using the Vicorder system (Skidmore, Bristol, UK) [25, 26]. Carotid to femoral pulse wave velocity (cfPWV) will be used to estimate arterial stiffness. The Vicorder system provides a non-invasive non-operator dependent method of obtaining cfPWV using a volume displacement method. Patients will be allowed to rest in a supine 30° head tilt position for 5 minutes prior to inflating a 100-mm-wide blood pressure cuff on the non-dominant arm to determine peripheral blood pressure. A 30-mm-wide partial cuff will be placed on the neck at the level of the carotid artery and a 100-mm-wide blood pressure cuff will be placed around the proximal thigh. The distance between the mid-clavicular point and the mid-point of the thigh cuff will be measured and entered in the Vicorder instrument as the aortic path length. The neck and thigh cuffs will then be inflated to 60 mm Hg and the Vicorder instrument will utilise the resultant oscillometric signal to extract the pulse waveforms and pulse transit time to calculate cfPWV. The mean value of three consistent recordings will be used for subsequent analysis. Inconsistent values will be re-analysed by a senior independent examiner not involved in taking the measurements to determine the validity of each measurement.

### Randomisation

Randomisation will be undertaken using the independent telephone-based randomisation system of the Primary Care Clinical Research and Trials Unit at the University of Birmingham (which is fully accredited by the NIHR as a trials unit). We will employ block randomisation by CD4 + CD28null cell percentage stratification (cut-off 40 %). The randomisation will use mixed blocks of random size (two, four or six) not known to the research team, therefore, minimising any risk of selection bias.

### Treatment

Patients randomised to the treatment arm will receive 2 g of valaciclovir orally four times a day. The dose will be reduced appropriately depending on renal function (Table 3). The study is open label and valaciclovir will be used off the shelf with no modifications to the packaging or labelling of the product. Patients will be asked to return unused tablets at each monthly visit to monitor compliance with medication. Patients randomised to the control arm will receive no additional treatment. Safety blood tests will be conducted monthly for the duration of treatment for the patients randomised to valaciclovir and these will comprise a full blood count, urea and electrolyte levels, and liver function tests. In the event of toxicity of grade 2 or less (scored using the National Cancer Institute (NCI) Common Terminology Criteria for Adverse Events version 4.0), the adverse event will be discussed with one of the investigators to determine whether drug administration should be temporarily withdrawn or the dose reduced. In the event of toxicity of grade 3 or more, the adverse event will be discussed with the principal investigator. In such a case, the expectation will be to withdraw drug administration for 1 week unless the adverse event is judged by the principal investigator to be unrelated to the study drug. Reintroduction of the drug will be based on a clinical review. The collection and reporting of data on adverse events and serious adverse events will be in accordance with EU directive 2001/20/EC and UK legislation.

**Table 3 Tab3:** Dose modification of valaciclovir according to creatinine clearance

Creatinine clearance (CrCl ml/min)^a^	Valaciclovir dose
>75	2 g four times a day
51–75	1.5 g four times a day
26–50	1.5 g three times a day
10–25	1.5 g two times a day

^a^Tests performed within 6 months of the pre-baseline visit can be used for this assessment

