## Background

The anti-neutrophil cytoplasmic antibody (ANCA) associated vasculitides (AAV) are a group of rare systemic autoimmune inflammatory chronic disorders that include granulomatosis with polyangiitis (Wegener’s granulomatosis) [1], microscopic polyangiitis, renal limited vasculitis and eosinophilic granulomatosis with polyangiitis (Churg–Strauss syndrome) [2]. AAV are characterised by necrotising inflammation affecting small to medium-sized blood vessels leading to end organ damage commonly affecting the kidneys, lungs and upper airways. They range in severity from localised disease affecting the upper airways to life-threatening involvement giving rise to multi-organ failure [3].

Over the last few decades, survival has greatly improved from 20 % at 2 years to 78 % at 5 years following diagnosis [4, 5]. However, survival remains below that of the healthy population with infection, cardiovascular disease (CVD) and malignancy being the most common causes of death.

Recently the role of T cells in AAV pathophysiology and exacerbation of tissue damage has gained attention. An increased percentage of CD4 T cells that have lost expression of the co-stimulatory molecule CD28 (CD4 + CD28null cells) have been reported in AAV [6]. Loss of CD28 implies repeated antigen exposure and, in a previous study, we demonstrated that this phenotype in AAV is driven by latent Cytomegalovirus (CMV) infection [7]. An expanded CD4 + CD28null cell population in this study was associated with an increased risk of infection and increased mortality in patients with AAV. In renal transplant recipients, the presence of CD4 + CD28null cell expansions is associated with a reduced response to antigenic challenge [8] and in elderly donors this pattern is also associated with frailty, reduced response to the influenza vaccine and increased mortality [9, 10]. In addition, CMV has been linked to a declining immune system associated with advancing age, a concept termed ‘immunosenescence’ [11].

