	Documentation that female patients of child-bearing potential are not pregnant and are using an appropriate form of contraception
	Written informed consent for study participation
Exclusion criteria	
	Stage 5 CKD (estimated glomerular filtration rate (eGFR) <15 ml minute^-1^ 1.73 m^-2^); tests performed within 6 months of pre-baseline visit can be used for this assessment
	Other significant chronic infection (HIV, hepatitis B, hepatitis C or tuberculosis)
	B-cell depleting therapy within 12 months or T-cell depleting therapy within 6 months
	Treatment with anti-CMV therapies in the last month
	Underlying medical conditions, which in the opinion of the investigator place the patient at unacceptably high risk for participating in the study
	Inability to participate fully or appropriately in the study

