**Fig. 1 Fig1:**
[figure not shown]
SPIRIT figure showing study’s schedule of enrolment, intervention and assessment. *M0* baseline visit, *M1* to *M12* month 1 to month 12, *qPCR* quantitative polymerase chain reaction. *Safety blood tests will be performed only on treatment group

After providing written informed consent, the patients will undergo an initial pre-baseline visit. During this visit, a 5-ml blood sample will be drawn, which will be used to determine the percentage of CD4 + CD28null cells. This value will be utilised in the randomisation of patients as explained below.

At the baseline, 6-month and 12-month visits, a total of 50 ml of blood will be drawn in addition to a 50-ml sample of urine. The samples will be used to determine CMV viral copies by DNA PCR in blood and urine (primary outcome), the proportion of CD4 + CD28null cells in peripheral blood by flow cytometry (secondary outcome), the concentration of soluble markers of inflammation (Table 1) in peripheral blood (secondary outcome) and immune assessments and T-cell phenotyping as detailed in the exploratory outcomes (Table 1). Excess sample will be stored appropriately. Blood pressure and arterial stiffness measurements will also be carried out at the baseline, 6-month and 12-month visits as detailed below.

During the remainder of the monthly visits, a 10-ml blood sample will be drawn in addition to a 50-ml sample of urine, which will be used to determine CMV viral copies by DNA PCR in blood and urine (primary outcome). Excess sample will again be stored appropriately. In addition, safety blood tests as defined below will be performed monthly for the duration of treatment for those patients randomised to receive the drug.

Appointments will be scheduled on monthly with an allowance of 10 days either side of the estimated due date of the monthly appointment to allow for patient convenience and flexibility. The overall treatment period (or control period) of 6 months will also be subject to the same 10-day rule to avoid excessive movement of the length of treatment.

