### Trial management and monitoring

The trial will be coordinated by the TMG (principal investigator, co-investigators and statistical advisor) in conjunction with the NIHR/WT CRF. A trial steering committee (TSC) that will include the TMG as well as two independent consultant nephrologists not involved in the study or regular review of patients recruited in the trial will provide the overall supervision of the trial. The TSC will oversee trial progress, protocol compliance, patient safety and review of updated information. Part of the role of the TSC will be to review safety data after the first ten patients have completed treatment. As this is a small proof-of-concept study with a short follow-up, no data monitoring committee will be formed, as agreed with the sponsor. Any protocol amendments will be submitted to the sponsor and relevant regulatory bodies for approval prior to implementation and trial participants will be informed of any protocol modifications. The University of Birmingham will conduct regular audit visits in its capacity as the trial sponsor to ensure compliance with the protocol and adherence to GCP and regulations.

The integrity of data entry will be ensured using a trial-specific Data Input Quality Control standard operating procedure (Trial Master File, University of Birmingham). Samples will be anonymised and all analyses will be undertaken on anonymised datasets with study identifiers replacing personal data. All personal details will be kept on NHS secure password-protected servers within UHB NHS Trust. Anonymised data will be transferred to password-protected servers in the University of Birmingham for analysis. No data will be stored on computer hard drives. All staff have confidentiality clauses in their honorary and substantive contracts.

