## Trial status

As at the time of submission, the CANVAS study is in the process of patient recruitment.

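### The Table 3 footnote permits the starting valaciclovir dose to be set from a creatinine clearance up to 6 months older than the pre-baseline visit

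*Protocol article*

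**What the plan says.** The Treatment section sets the dose at 2 g four times a day, lowered according to renal function. Table 3 gives four rows by creatinine clearance: above 75, 51–75, 26–50 and 10–25 ml/min. The footnote on the clearance column reads "Tests performed within 6 months of the pre-baseline visit can be used for this assessment".

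Table 2 attaches the same allowance to the exclusion of patients with eGFR below 15: "tests performed within 6 months of pre-baseline visit can be used for this assessment".

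On monitoring, the Treatment section says "Safety blood tests will be conducted monthly for the duration of treatment for the patients randomised to valaciclovir", and these tests include urea and electrolytes. Monthly visits have "an allowance of 10 days either side of the estimated due date of the monthly appointment" (Schedule of assessments). For the pre-baseline visit, the text mentions one 5-ml sample, used for the CD4+CD28null percentage that enters randomisation. The uses it lists for the baseline samples are CMV PCR, flow cytometry, soluble markers and immune assays. No visible sentence requires a creatinine close to the first dose.

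**The concern.** The table makes clearance the determinant of dose, while the footnote allows that clearance to be out of date. Baseline follows pre-baseline, so a result at the edge of the window is more than 6 months old when treatment starts. Because Table 2 has the same window, one old result may settle both eligibility and dose.

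The Background describes the disease as "leading to end organ damage commonly affecting the kidneys, lungs and upper airways", and entry is open down to an eGFR of 15, so every row of Table 3 can be occupied. What is at stake is dose accuracy and the safety of individual patients on valaciclovir. An investigator who followed the footnote to the letter and started a patient on the wrong row would have complied with the protocol.

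**Working it through.** The plan gives no figure of its own for this point, so the check uses Table 3 and the visit schedule.

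**1. Daily dose by row (Table 3)**
- Above 75 ml/min: 2 g × 4 = 8 g
- 51–75: 1.5 g × 4 = 6 g
- 26–50: 1.5 g × 3 = 4.5 g
- 10–25: 1.5 g × 2 = 3 g

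**2. One row wrong, relative to the tabulated dose**
- Too high: 8/6 − 1 = 33%; 6/4.5 − 1 = 33%; 4.5/3 − 1 = 50%. The largest relative excess falls in the lowest clearance row.
- Too low: 1 − 6/8 = 25%; 1 − 4.5/6 = 25%; 1 − 3/4.5 = 33%.

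**3. Change in clearance needed to cross a cut-off**
- Near a cut-off a small fall is enough: 80 to 70 is 10/80 = 12.5%; 55 to 48 is 7/55 = 13%; 30 to 24 is 6/30 = 20%.
- Further away it takes more: from 100 down to 75 is 25/100 = 25%; from 38 down to 25 is 13/38 = 34%.

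**4. How long a wrong row could last.** This step is conditional: it assumes that the month-1 visit is the first recheck and that its result is acted on. Month 1 is about day 30, so the 10-day allowance gives day 20 to 40. The excess is 1.5 to 2 g/day (6 − 4.5, 4.5 − 3 and 8 − 6), so the total is 1.5 × 20 = 30 g to 2 × 40 = 80 g. A baseline test that was acted on would remove this.

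**5. How many patients.** The document gives no distribution of clearance, no between-test variation and no rate of decline, so no count follows from it. To show how far any count depends on assumption:
- Earlier clearance was taken as Normal with mean 50–70 and SD 20–25 ml/min, kept if at least 12.
- Later clearance was the earlier value × exp(Normal(d, s)), with s from 0.07 to 0.20 and d of 0 or −0.05.
- Rows were cut at 25.5, 50.5 and 75.5, with 2,000,000 draws per scenario.
- All 25 treated patients were assumed to be dosed from an old test.

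Results per 25 patients:
- Too high, gross: 1.3 to 5.3.
- Too high, after subtracting the crossings seen at s = 0.07 and d = 0 (which a fresh test might not remove): 0 to 3.9.
- Too low, with no drift: 1.24–1.40 at s = 0.07 and 3.1–3.9 at s = 0.20.
- Mean starting dose: off by at most about 0.06 g/day with no drift, and 0.11–0.21 g/day too high with d = −0.05.

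**The case against.** The strongest case on the other side has four parts.

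- **The footnote only permits.** The governing instruction is to lower the dose as renal function requires. An investigator who held a current result and chose an older, higher one would hardly be doing that. This stands: nothing forces the use of an old result, and a newer one is equally allowed.
- **A baseline test may exist.** The legend of Fig. 1 shows that the figure schedules the safety bloods, and the figure is not shown. This also stands, so it cannot be said that a baseline creatinine is missing. If one is taken, rewording the footnote brings it into line with practice.
- **Safeguards elsewhere.** Patients must have had no documented disease activity for at least 6 months, roughly the permitted age of the test, and they attend one clinic with long-term follow-up. On drug, urea and electrolytes are checked monthly, and the dose can be lowered or withheld for toxicity. Two independent nephrologists sit on the steering committee, which reviews safety after ten patients complete treatment. These limit how often a wrong row occurs and how long it lasts. They do not make the starting result current, and monthly tests act only once dosing has begun.
- **The Background sentence on kidney damage is general.** It does not show short-term decline in patients in stable remission. Agreed.

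A reader might infer from the footnote that several of the 25 treated patients will be systematically overdosed. The documents do not support that. The counts in step 5 rest wholly on assumed inputs, the net range includes zero, and its upper end needs the widest variation, a 5% mean fall and every patient dosed from an old test. With no drift, about as many patients start too low as too high. A reader might also infer that the footnote governs dose changes during treatment. It does not: a test dated from the pre-baseline visit can inform only the starting dose.

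**Conclusion.** The point holds as a minor matter of patient safety. A stated rule lets a dose that depends on clearance be started from an out-of-date clearance. The size per affected patient follows from Table 3 without assumptions: one row too high is 33% or 50% above the tabulated daily dose, and one row too low is 25% or 33% below. The number of patients affected is unknown and may be zero, and no harm rate can be given. The exposure of 30 to 80 g applies only if month 1 is the first recheck. The point does not touch the sample size, power or significance level.

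**What to change.** Reword the Table 3 footnote along these lines: *The starting dose is set from a creatinine taken at the pre-baseline or baseline blood draw, with the result available before the first dose.* Keep the 6-month window for pre-screening only, and confirm an eGFR of at least 15 on the pre-baseline sample before randomisation. If Fig. 1 or the full protocol already schedules a baseline creatinine, the footnote need only say that this result sets the dose.

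The cost is one extra tube at a draw that already takes place. The result must be back before dosing, and an occasional patient will be excluded late. It also needs a minor amendment: "Any protocol amendments will be submitted to the sponsor and relevant regulatory bodies for approval prior to implementation". At submission of the article "the CANVAS study is in the process of patient recruitment", so the change can help only patients who have not yet started treatment.

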### Sample size calculation and planned statistical analyses

In an immunocompetent elderly population, CMV reactivation occurred in 90 % at 6 months [18]. It is expected that CMV reactivation will be at least that in our immunosuppressed population. Information for dosing regimens using antiviral prophylaxis in renal transplant recipients has demonstrated over 90 % suppression of CMV reactivation. Our sample size assumes 90 % reactivation in the control limb and a conservative estimate of 50 % reactivation in the treated group. The estimated sample size is 50 patients, 25 patients in each arm, based on 80 % power at a significance level of *p* < 0.05 (two-tailed test).

All analyses will be performed using the intention-to-treat principle. Baseline covariates will be compared between the two arms to observe the balance and the success of randomisation. The primary analysis will test the hypothesis that there is no difference in the proportion of patients with CMV reactivation between those receiving antiviral prophylaxis compared with those receiving usual treatment. For the secondary outcomes, comparisons will be made between groups using absolute measures of immune function and change between data at entry and end of treatment within groups. Missing data will be dealt with by simple imputation if missing randomly. Where data are missing systematically, appropriate statistical models will be applied to avoid attrition bias. A full statistical analysis plan will be written and approved prior to data analysis.

A safety analysis will be performed on all treated patients. The number of events and incidence of adverse events by system organ class will be summarised and the relationship to the treatment noted.

The final report will follow the CONSORT 2010 guidelines and will be published in a peer-reviewed journal. Authorship will be based on the International Committee of Medical Journal Editors guidelines. Results will be communicated to study participants and patient groups through presentations at patient and carer group meetings.

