## Methods/design

This is a single-centre open-label randomised controlled trial of oral valaciclovir treatment (2 g four times a day; reduced appropriately depending on renal function) for 6 months versus no additional treatment, in CMV seropositive patients with stable AAV, followed by a 6-month follow-up period. No placebo will be used.

The primary outcome is the proportion of patients with CMV reactivation, as assessed by measurable viral load on quantitative blood and urine CMV polymerase chain reaction (PCR). The secondary outcomes are safety, as defined by adverse events sufficient to stop treatment with valaciclovir, change in the proportion of the CD4+ CMV-specific T-cell population (defined as CD4 + CD28null cells) and change in soluble markers of inflammation from baseline to 6 months (Table 1). Further tertiary and exploratory outcomes include persistence of the effect of valaciclovir on the proportion of CD4 + CD28null cells at 6 months post completion of treatment, change in the immune phenotype of CD4+ T cells and change in blood pressure and arterial stiffness parameters from baseline to 6 months (Table 1).

**Table 1 Tab1:** Study endpoints

	Description	Specific measurement variable
Primary outcome		
	Proportion of patients with CMV reactivation	Quantification of viral DNA copies in blood and urine by quantitative polymerase chain reaction (qPCR)
Secondary outcomes		
	Safety	Number of adverse events and incidence of events by system organ class
		Adverse events sufficient to stop treatment with study drug
	Change in the proportion of CD4 + CD28null cells from baseline to 6 months	Proportion of CD3 + CD4 + CD28- T cells in peripheral blood
	Change in the concentration of soluble markers of inflammation from baseline to 6 months	Concentration of IL-2, tumour necrosis factor alpha (TNF-α), IFN-γ, IL-6, IL-10, IL-17 and highly sensitive C-reactive protein (CRP) in peripheral blood
Tertiary outcome		
	Persistence of valaciclovir effect on the proportion of CD4 + CD28null cells from 6 months to 12 months	Proportion of CD3 + CD4 + CD28- T cells in peripheral blood
Exploratory outcomes		
	Change in immune phenotype of CD4+ T cells from baseline to 6 months	Proportion of CD4 + CD28null cells secreting IFN-γ, IL-2, TNF-α, IL-5 and IL-10 in response to CMV lysate stimulation
		Proportion of CD4 + CD28null cells expressing the inhibitory receptors PD-1, TIM-3, CTLA-4 and lymphocyte activation gene 3 (LAG-3)

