### Schedule of assessments

Patients will attend for a total of 14 visits over a period of just over 12 months (Fig. 1). Evaluation of CMV reactivation by deoxyribonucleic acid (DNA) PCR of blood and urine will be done monthly. Evaluation of the tolerability of the drug and adverse events will occur monthly. Immune assessments as detailed below and in Table 1 will be performed at entry, 6 months and 12 months (Fig. 1).

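### The immune secondary outcomes are defined as change from baseline, but the stated analysis most naturally compares arms on unadjusted absolute values and looks at change within arms; a baseline-adjusted between-arm comparison should be named

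*Protocol article*

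**What the plan says.** In the protocol article, Table 1 (Methods/design) lists two immune secondary outcomes, both defined as change: "Change in the proportion of CD4 + CD28null cells from baseline to 6 months" and "Change in the concentration of soluble markers of inflammation from baseline to 6 months". The second covers seven soluble markers.

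The section on sample size and planned analyses then fixes how the secondary outcomes are to be handled: "comparisons will be made between groups using absolute measures of immune function and change between data at entry and end of treatment within groups". It names no baseline-adjusted between-arm estimate. The same section promises a full statistical analysis plan before data analysis; that plan is not shown.

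Baseline data will exist. Under Schedule of assessments, the immune assessments "will be performed at entry, 6 months and 12 months". The CD4+CD28null percentage is also measured at the pre-baseline visit: "This value will be utilised in the randomisation of patients as explained below". The Randomisation section specifies "block randomisation by CD4 + CD28null cell percentage stratification", with a cut-off of 40%.

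**The concern.** The endpoint and its analysis do not line up. If arms are contrasted on absolute values and change is looked at arm by arm, the quantity in Table 1 is never compared between the randomised groups.

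The two halves of the sentence have different weaknesses. A change inside one arm mixes any drug effect with drift, regression to the mean and changes in background treatment; removing these is what the control arm is for. The protocol's own Background describes a gradual accumulation of these cells under CMV, so a change common to both arms is plausible. The between-arm contrast of absolute values is free of that problem, but it discards baseline information that the trial collects and considers important enough to stratify on.

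The Background hypothesises that valaciclovir will ameliorate the CD4+CD28null expansion, and the Discussion expects the results to enable larger studies. An imprecise or ambiguous result on this outcome would weaken that use.

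**Working it through.** **The plan's own figure.** The only stated calculation is for the primary outcome: 90% against 50% reactivation, 80% power, two-sided 0.05. The usual two-proportion formula gives 20 per arm, and 25 per arm with the continuity correction, which matches: "The estimated sample size is 50 patients, 25 patients in each arm". It does not bear on this point, except that it fixes 25 per arm. No calculation is given for the secondary outcomes.

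**Inputs.** From the document: 25 per arm, and baseline and 6-month values for each marker. Assumed, because the documents give neither an SD nor a correlation: equal SD at both visits, a baseline to month-6 correlation r from 0.3 to 0.9, a true month-6 difference of 0.4 SD, and a two-sided 0.05 test.

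**Variance of the outcome, in units of SD².**

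- Month-6 value alone: 1
- Change compared between arms: 2(1 − r)
- ANCOVA on baseline: 1 − r²

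At r = 0.7 these are 1, 2 × 0.3 = 0.60 and 1 − 0.49 = 0.51. The unadjusted variance is therefore 1/0.51 = 1.96 times that of ANCOVA.

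**Power for 0.4 SD.** The noncentrality is 0.4 × √(25/2) / √v, with v the variance above. For the month-6 value alone this is 0.4 × 3.536 = 1.414, which gives 28% from the noncentral t distribution. For ANCOVA:

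| r | 1 − r² | Noncentrality | Power, ANCOVA | Power, month 6 only | Variance ratio |
|---|---|---|---|---|---|
| 0.3 | 0.91 | 1.48 | 31% | 28% | 1.10 |
| 0.5 | 0.75 | 1.63 | 36% | 28% | 1.33 |
| 0.7 | 0.51 | 1.98 | 49% | 28% | 1.96 |
| 0.8 | 0.36 | 2.36 | 64% | 28% | 2.78 |
| 0.9 | 0.19 | 3.24 | 89% | 28% | 5.3 |

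The degrees of freedom spent on covariates hardly alter these figures.

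**Difference detectable with 80% power** (normal approximation), for month-6 value / between-arm change / ANCOVA: 0.79/0.94/0.76 SD at r = 0.3, 0.79/0.79/0.69 at r = 0.5, 0.79/0.61/0.57 at r = 0.7 and 0.79/0.35/0.35 at r = 0.9. Comparing unadjusted change is worse than ignoring baseline when r is below 0.5. ANCOVA is the best of the three at every r shown.

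**Validity.** Randomisation makes the expected baseline equal in the two arms. The expected difference in month-6 values therefore equals the expected difference in change. The absolute comparison targets the right effect, only with more noise.

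**Separate within-arm tests.** Suppose that both arms have the same true change and that each within-arm test rejects with probability p. Exactly one arm is then significant with probability 2p(1 − p):

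- p = 0.05 (no change in either arm): 2 × 0.05 × 0.95 = 9.5%
- p = 0.2 or 0.8: 2 × 0.2 × 0.8 = 32%
- p = 0.5: 2 × 0.5 × 0.5 = 50%, the maximum of the expression

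These figures apply only if efficacy were inferred from such a pattern. The protocol does not say that it will be.

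**The case against.** **The sentence has a second reading.** It can be parsed as between-group comparisons that use both absolute measures and each group's change. That fits Table 1 better, and the text does not say that change is assessed only within arms. This stands: the within-arm reading is the more natural one, not the only one. But the two readings give different analyses, so the ambiguity itself needs removing, and neither reading names a baseline-adjusted estimate.

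**There is a valid comparison.** A reader might infer that the trial has no valid randomised comparison of these outcomes. The documents do not support that: the month-6 contrast is valid, and stratifying at 40% limits gross baseline imbalance on CD4+CD28null. What it lacks is efficiency.

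**The protocol does not adopt a significant-in-one-arm rule.** A reader might also infer that efficacy will be judged by contrasting within-arm p-values. The text only mentions within-group change, and the 50% figure is a mathematical worst case. This stands in full.

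**The gain is uncertain.** At r = 0.3 it is 3 percentage points of power (28% to 31%), and nothing in the documents supports a high r for the seven soluble markers. This also stands.

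**Model detail belongs in the analysis plan.** Covariates and transformations are commonly left there, and their absence from an article would be no finding. Here, however, the article does state a method, and on its natural reading that method does not match the endpoint. A later plan would have to inherit the mismatch or depart from the protocol.

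**Conclusion.** The point holds in a limited form. Table 1 and the stated analysis do not match on the more natural reading of the sentence, and under either reading the treatment effect on these outcomes is not clearly specified. The consequence is lost precision and an unclear estimate, not bias in the month-6 comparison.

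The loss rests on the assumed r, equal SDs and a 0.4 SD difference. It runs from slight at r = 0.3 to large at r = 0.9, where ANCOVA has 89% power and the unadjusted comparison 28%.

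The point is worth correcting but is below must-fix. It concerns secondary outcomes of a 50-patient proof-of-concept trial, and no data are lost. The primary analysis is already a direct between-arm comparison, and nothing here calls for a change to it.

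**What to change.** Reword the sentence on secondary outcomes along these lines: for each secondary immune outcome, the treatment effect is the between-arm difference at 6 months, estimated by ANCOVA with terms for arm, the baseline value of that outcome and the randomisation stratum, on the log scale where the outcome is skewed, and reported with a 95% confidence interval; changes within each arm are descriptive only and are not used to infer a treatment effect.

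With the baseline value in the model, the estimated arm effect is the same whether the dependent variable is the month-6 value or the change (on the same scale), so Table 1 can stay as it is.

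The cost is wording in the protocol and the matching text in the analysis plan, settled before data analysis. It needs no new visit, sample or assay.
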